### Data management

Data collection will be performed locally and anonymised for name and date of birth in an independent database, then submitted to the Department of Medical Biometry Heidelberg (IMBI). An interim analysis is planned after 2, 5 and 10 years, and it is estimated to include at least 80 patients per year. All results of the GCRR, including epidemiological data, surgical techniques, material for CP, complications, risk factors and long-term outcome, will be published and/or reported at respective scientific meetings. This study is indexed in the German Clinical Trials Register (DRKS-ID: DRKS00007931). The Universal Trial Number (UTN) is U1111–1168–7425.

### Statistics

Endpoints will be evaluated using descriptive statistics, and the key figures of the distributions will be presented in tables. Univariate analyses will allow for a first overview of potentially influential factors. Depending on the composition of the data, χ^2^, Mann-Whitney U and t tests, or Pearson or Spearman correlation coefficients, will be conducted. Relationships between multiple independent variables on the dependent variable(s) will be tested using multivariate regression analysis. Missing values will be replaced and estimated using multiple imputations. Furthermore, sensitivity analysis will be executed using complete-case analysis.

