**Methods:**

All patients undergoing cranioplastic surgery in participating centres will be invited to join the registry. Technical methods, materials, medical history, adverse events and clinical outcome measures, including modified Rankin scale and EQ-5D, will be assessed at several time points. Patients will be accessible to inclusion either at initial decompressive surgery or when cranioplasty is planned. Scheduled monitoring will be carried out at time of inclusion and subsequently at time of discharge, if any readmission is necessary, and at follow-up presentation. Cosmetic results and patient satisfaction will also be assessed. Collected data will be managed and statistically analysed by an independent biometric institute. The primary endpoint will be mortality, need for operative revision and neurological status at 3 months following cranioplasty.

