**Trial registration number:**

This trial is indexed in the German Clinical Trials Register (DRKS-ID: DRKS00007931). The Universal Trial Number (UTN) is U1111-1168-7425.

Strengths and limitations of this studyThe German Cranial Reconstruction Registry (GCRR) is a prospectively conducted, multicentre, international, open registry study in which patients will be observed long term.Owing to the prospective international nature (Germany, Austria, Switzerland), a very wide range of cranioplastic treatment options will be detected. Similar publications and studies are only monocentric.The registry includes patients with decompressive craniectomies in a wide range of acute diseases (eg, traumatic brain injuries, space-occupying cerebral infarction, subarachnoid and intracerebral haemorrhage, etc) as well as destructive or osteolytic bone tumours.A limitation of the study is that the GCRR is not a randomised study, but only a pure observational study. Specific treatment strategies will not be compared against each other.One of the strengths as well as simultaneous limitation of this study is the planned long observation period of up to 10 years. There is the possibility of a high number of participants lost to follow-up.

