**Figure 1 BMJOPEN2015009273F1:**
[figure not shown]
Study protocol of the German Cranial Reconstruction Registry (GCRR): using a structured questionnaire (for physicians and patients), patients’ clinical pathways will be monitored in four steps, from the craniectomy, over the cranioplasty and up to the long-term follow-up.

*Craniectomy*: The first part of the CRF covers the initial surgery, craniectomy. In addition to patient data (sex, age) and diagnosis, the initial neurological status (Glasgow Coma Scale (GCS), National Institute of Health Stroke Scale (NIHSS), World Federation of Neurosurgical Societies Scale (WFNS), Hunt and Hess), medical history (American Society of Anesthesiologists (ASA) Physical Status Classification), comorbidities (eg, diabetes, arterial hypertension, coagulopathy) and risk factors (eg, smoking status, drugs), is recorded. In addition, surgical data such as localisation of skin incision, trephination size and localisation, dura opening and closure technique (duraplasty) as well as materials used (eg, suture material and technique, drainage), are registered. Moreover, the experience of the surgeon, duration of operation, amount of blood loss and any perioperative antibiotic therapy given, will be documented. Finally, the storage of the bone and perioperative complications are listed. The initial observation period following DC (part 1) will end with discharge of the patient, where neurological status is recorded (Glasgow Outcome Scale (GOS), modified Ranking Scale (mRS), NIHSS).

*Cranioplasty*: The second part of the CRF covers all particular details of CP. Here, new patients can be included independently of the prior procedure, for example, when operated earlier at another institution. Again, preoperative data and the current neurological status are recorded. Particular attention is paid to the size of craniotomy and the type of CP (autologous vs alloplastic). All types of materials are included (eg, plastic, ceramic, titanium alloy, etc) and will be distinguished between patient-specific and hand-made CP. Details for fitting and fixating the material, simultaneous implantation of a CSF-shunt as well as standard parameters (suture material, size and number of drainage apparatus, perioperative antibiotics) will be covered. Similar to during the DC procedure, operating duration and amount of blood loss will be captured.

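### Complete-case analysis, the only sensitivity analysis named beside multiple imputation, cannot show whether outcome rates survive outcome-dependent loss to follow-up

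*Protocol article*

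**What the plan says.** The Statistics section of the protocol article gives missing data two sentences. The main method is fixed as "Missing values will be replaced and estimated using multiple imputations". The check on it follows: "Furthermore, sensitivity analysis will be executed using complete-case analysis". The section names no other sensitivity analysis and states no missingness assumption. It also says that endpoints are to be summarised descriptively, with univariate tests and multivariate regression to look for influential factors.

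The strengths and limitations box, printed below the trial registration number, lists the "planned long observation period of up to 10 years" as both a strength and a limitation, and adds: "There is the possibility of a high number of participants lost to follow-up". No rate is given, and the box does not say that loss would depend on how patients fare.

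The abstract defines the endpoint: "The primary endpoint will be mortality, need for operative revision and neurological status at 3 months following cranioplasty". The Case report form section adds a 12-month form and annual forms after it, which record revision procedures, GOS, mRS, SF-12, EQ-5D and the cosmetic result.

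**The concern.** A sensitivity analysis should vary the assumption most likely to fail. The limitation that the article itself raises is loss to follow-up, so the natural question is what happens to the results if lost patients differ in outcome from those seen. Complete-case analysis does not ask that question. For an outcome rate, it takes those seen to represent everyone. Standard imputation takes those seen to represent everyone with the same measured characteristics. Neither allows lost patients to differ in ways that were not measured.

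Outcome-dependent loss is an inference from the design, but a plausible one. The patients have severe infarction, haemorrhage or trauma, and severe disability may make annual attendance harder. The Cranioplasty part of the form accepts that a patient may have had the craniectomy at another hospital, so a later revision could also be done elsewhere and go unseen. The direction is not obvious, because patients with a problem may also be the ones who come back.

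At stake are the registry's published revision rates and functional outcomes. They could be labelled robust because two methods agree, when both share the same error.

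**Working it through.** The plan states no loss rate or missingness model, so there is no figure to reproduce. Every loss rate and strength of dependence below is an assumption.

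**1. Simple illustration (revision rate)**

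Inputs, all assumed: share lost L = 0.30; rate among those seen = 0.20; rate among those lost between 0.10 and 0.40.

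- Complete-case estimate: 0.20.
- Missing-at-random imputation without strong predictors of the outcome: also about 0.20.
- True rate = (1 − L) × rate seen + L × rate lost:
  - low: 0.7 × 0.20 + 0.3 × 0.10 = 0.17
  - high: 0.7 × 0.20 + 0.3 × 0.40 = 0.26

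**2. Closed form for outcome-dependent loss**

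Inputs: a true event rate p = 1/3, borrowed from the cranioplasty complication rate in the Introduction and used only as an example; overall loss 30%. With loss l1 in patients with the event and l0 in those without, the rate among those seen is p(1 − l1) / [p(1 − l1) + (1 − p)(1 − l0)].

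- l1 = 40%, l0 = 25%: 0.200 / 0.700 = 28.6%
- l1 = 50%, l0 = 20%: 0.167 / 0.700 = 23.8%
- l1 = 20%, l0 = 35%: 0.267 / 0.700 = 38.1%

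The error can go either way.

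**3. Does imputation do better than complete-case?**

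This was simulated with n = 800 (80 patients per year for 10 years, from the Data management section), one covariate related to the outcome, 10 imputations and 200 repetitions. Strength of dependence is the log-odds of loss per unit of the covariate, or for event versus no event.

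| Loss depends on | Lost | Truth | Complete-case | Imputation |
|---|---|---|---|---|
| nothing | 25% | 33.1% | 33.1% | 33.1% |
| covariate (0.5) | 26% | 33.2% | 31.7% | 33.0% |
| outcome (0.8) | 31% | 33.0% | 27.5% | 27.7% |
| outcome (1.2) | 34% | 32.9% | 23.7% | 24.1% |
| covariate (0.5) and outcome (0.8) | 32% | 33.2% | 25.9% | 27.3% |

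When loss depends on the measured covariate, imputation corrects the error and complete-case does not. When loss depends on the outcome alone, the two agree to within half a point and both are about 5 to 9 points too low. In the mixed case they differ by 1.4 points, but imputation is still about 6 points low. The gap between the methods therefore says little about the distance of either from the truth.

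**4. What a delta-adjusted analysis would show**

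Observed rate 1/3, so odds 0.5. Doubling the odds in the missing patients gives odds 1.0, a rate of 50%. At 30% lost, the overall rate is 0.7 × 33.3% + 0.3 × 50% = 38.3%. The extreme bounds at 30% lost are 0.7 × 33.3% = 23.3% and 23.3% + 30% = 53.3%.

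In step 1, the assumed 10% to 40% risk corresponds to odds of 0.111 and 0.667 against 0.25 in those seen. These are odds ratios of 0.44 and 2.67, or shifts of about −0.8 and +1.0 on the log-odds scale.

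**The case against.** The strongest reply is that imputation with a complete-case check is ordinary practice for an observational registry that compares no treatments, and that an analysis plan not shown here may add more. Part of this stands: the choice is conventional, and the point is an improvement, not a fatal flaw. But purely descriptive endpoints do not weaken the point. A crude or imputed rate is exactly what outcome-dependent loss distorts.

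A second reply concerns regression. If missingness depends on covariates but not on the outcome given those covariates, complete-case coefficients remain valid even where standard imputation may not. Logistic odds ratios also survive loss that depends only on the outcome. This stands. It would be wrong to say that complete-case analysis always needs the stronger assumption, and for the search for influential factors it is a useful check. The point here is confined to outcome rates.

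Two stronger readings are tempting and not supported:

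- *A reader might infer that the article predicts informative loss.* It names a possibility of high loss and says nothing about its relation to outcome.
- *A reader might infer that values which cannot exist will be imputed*, such as quality of life after death, "World Federation of Neurosurgical Societies Scale (WFNS), Hunt and Hess" in patients without subarachnoid haemorrhage, or forms not yet due. The article speaks only of missing values, and such blanks are not ordinarily counted as missing. The form records diagnosis and type of cranioplasty, from which applicability can be worked out, and rules of this kind are commonly left to the analysis plan. Patients operated on earlier elsewhere are a different case: their craniectomy data exist but may be unavailable, and imputing them can be legitimate.

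**Conclusion.** The point holds for outcome rates. The one sensitivity analysis named does not test the risk that the article itself raises, and its agreement with multiple imputation would not establish robustness.

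The size cannot be fixed from the document. Under the assumed 30% loss, a reported 20% revision rate could stand for 17% to 26%. In the simulations with about 31% to 34% lost and loss depending on outcome alone, both methods fell about 5 to 9 points below a true rate near 33%. With little loss, or loss explained by measured characteristics, the problem shrinks or disappears. It matters most for the annual follow-up over up to 10 years, and probably less at 3 months, where less loss would be expected.

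**What to change.** Keep multiple imputation as the main analysis and complete-case analysis as a secondary check. Add a delta-adjusted (tipping-point) imputation for revision and for mRS at follow-up:

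- Shift the imputed log-odds of revision, and of a worse mRS, over a prespecified range in both directions. A range of about −0.8 to +1.0 would reproduce the revision illustration above.
- Report the rate at each shift, together with the share of patients lost at that visit. Where a conclusion rests on a rate, report the shift at which it would change.
- State the missing-at-random assumption of the main imputation.

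In the same sentence, make the scope of imputation explicit: death is scored in the category that mRS and GOS already have for it, and imputation is confined to values that were due and applicable in living patients. This clarifies the plan and does not correct a stated error.

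The cost is a few lines of text, one extra analysis run on imputations already made, and a wider reported range. No further patients, visits or data items are needed.

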### Registry reports

Results of the GCRR will be published by the Steering Committee and distributed to all participating centres following careful analysis by the IMBI.

## Discussion

DC and CP are of increasing importance in neurosurgery. While they both are standard neurosurgical interventions, and are supposed to be ‘simple’ and ‘extracerebral’ surgical procedures, complication rates are surprisingly high and there is definitely a lack of evidence.

The GCRR is designed as a multicentre prospective data collection to uncover risk factors of both procedures, thus minimising complication rates, especially regarding periprocedural wound infections, CSF leakages and reasons for surgical revisions, as well as improving long-term clinical and cosmetic outcome focusing on CP materials, reasons for revision surgeries and rehabilitation processes. The amount of data and variety of aspects covered by this registry will give new insight in DC and CP, enhancing our knowledge regarding these ‘easy’ operative procedures. Currently, DESTINY-R is evaluating the short-term and long-term risks and benefits of DC in patients with MCA infarction in a large population routinely treated in neurological and neurosurgical units.^30^ The GCRR takes a step forward since it is not limited to one disease entity, and features a procedure and follow-up procedure in great detail. The effectiveness of registries and long-term surveillance of neurosurgical implants has been well demonstrated with, for example, the UK shunt registry.^31^ By the acquisition of nearly 33 000 CSF shunt-related procedures, for example, the benefit of antibiotic-coated catheters could be proven.^32^ Similarly, a registry for CP surgeries called ‘UK Cranial Reconstruction Registry (UKCRR)’ was founded for the UK.^33^ Both the GCRR and UKCRR have had overlap in the planning phase and contents of both registries were harmonised. Inspired by these successful registry projects, now the GCRR will be initiated for Germany, Austria and Switzerland.
